#### 2.7.1. Standard Treatment Group (CEMR Group)

Submucosal injections must be administered with a solution commonly used at each institution. The injection time will be considered as the start time of the CEMR procedure.The lesion, including the surrounding non-tumor mucosa, should be strangled with a commercially available snare of any type or size, chosen at the discretion of each endoscopist. Bipolar snares can be used. However, EMR with the cap technique is not permitted. Although the following settings are recommended for high-frequency devices, adjustments may be made at each facility: Endo-Cut Q mode, effect 2, duration 1, interval 6 for the VIO 300D ERBE; Endo-cut Q, effect 2 for the VIO3. Specimen retrieval should be performed using a retrieval net, grasping forceps, or a snare at the discretion of the endoscopist. Intentional fragmentation is not allowed.

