#### 2.7.2. Trial Treatment Group (UEMR Group)

After deflating the stomach and duodenum, the duodenal lumen must be filled with saline solution. The start time of saline immersion will be considered the start time of the UEMR procedure. Gel immersion is not permitted in this case.The lesion, including the surrounding non-tumor mucosa, should be snared under saline immersion using a commercially available snare of any type or size, chosen at the discretion of each endoscopist. Bipolar snares can be used. Although the following settings are recommended for high-frequency devices, adjustments may be made at each facility: Endo-Cut Q mode, effect 3, duration 2, interval 4 for VIO 300D ERBE, and Endo-Cut Q, effect 3 for VIO3. Specimen retrieval was performed in the same manner as in CEMR.

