#### 2.7.4. Mucosal Closure of EMR Ulcer Bed

Commercially available standard clips with two arms will be used for complete mucosal closure. If closure with a standard clip is challenging, the line-with-clip method or an over-the-scope clip (OTSC) is permitted. If closure is performed using a device other than the standard clip, it is considered a failure of standard clip mucosal closure. The mucosal closure time will be calculated by subtracting the resection time from the total procedural time. Photographs will be captured after the completion of closure and before finishing the procedure.

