#### 2.7.5. Rescue Treatment in Case of Incompletion of Allocated Endoscopic Resection Method

If the allocated endoscopic resection method is attempted repeatedly and is not completed within 15 min from the beginning of treatment, the endoscopist may switch to an alternative treatment method, such as CEMR, UEMR, ESD, or surgical resection at their discretion. In this case, the protocol treatment will be discontinued, and the procedure will be considered a failure to achieve completion.

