CEMR: Time from the start of submucosal injection to the completion of mucosal closure.

UEMR: Time from the start of saline immersion to the completion of mucosal closure.

6.Resection time

The resection time is calculated only for cases with successful resection (per-protocol analysis).

CEMR: Time from the start of submucosal injection to the completion of lesion resection.

UEMR: Time from the start of saline immersion to the completion of lesion resection.

7.Mucosal closure time

The mucosal closure time is defined as the time obtained by subtracting the resection time from the total procedural time. Closure time is calculated only for cases with successful resection.

8.Complete mucosal closure rate

The complete mucosal closure rate is defined as the proportion of cases in which complete closure is achieved among all treated cases. Complete mucosal closure is considered if the EMR ulcer bed is not visible.

9.Complete mucosal closure rate with standard clips

Complete mucosal closure rate with standard clips is defined as the proportion of patients in whom mucosal closure is completed using only standard clips with two arms without using the clip-line method or OTSC. The number of treated patients is the denominator.

10.One-year duodenum preservation survival rate

The one-year duodenal preservation survival rate is defined as the proportion of patients in whom the duodenum is preserved without undergoing any surgical resection, and those who survive for one year after EMR. Any surgical duodenal resection and cause of death are considered events. If surgical resection occurs, information on the resected specimen will also be collected.

11.Device cost

The total cost is calculated for all treated cases and includes the cost of single-use devices (snare, ESD knife, hemostatic forceps, injection needle, injection fluid, submucosal injection fluid, clips, and OTSC) used during endoscopic resection. Device costs will be calculated based on Japanese reimbursement prices for single-use devices.

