A recent prospective observational study was conducted in Japan to evaluate the treatment of SNADETs ≤ 20 mm [12]. This study included 155 patients who underwent UEMR from multiple centers. The *en bloc* and histological complete resection rates were 89.8% and 66.9%, respectively, with a 1-year non-recurrence rate of 97.2%. However, our D-CURE trial has several strengths compared to previous studies. First, this is the first RCT conducted across 40 institutions in Japan, enabling the demonstration of safety and efficacy through random allocation and comparison, thus mitigating the possibility of selection bias observed in single-arm prospective trials. We aim to establish the efficacy, safety, and cost-effectiveness of UEMR based on robust results from the D-CURE trial. Additionally, the D-CURE trial includes mucosal closure as a component of the treatment protocol following resection. Mucosal closure has been shown to significantly reduce postoperative complications such as delayed bleeding and perforation by protecting the submucosal and muscular layers from bile and pancreatic juice. Although mucosal closure is considered essential, it is effective only when the ulcer bed is completely covered by the mucosa [34,35]. Although various closure methods using suturing devices have been reported, a simple and cost-effective method is preferred. Because the ulcer bed after UEMR tends to be smaller than that after CEMR, owing to the absence of submucosal injection, suturing with standard clips may be easier. Therefore, in this study, we specified a protocol to use standard clips as the primary method for closure. This approach may highlight differences in the complete mucosal closure rate achieved with standard clips between CEMR and UEMR.

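### The only economic endpoint is index-procedure device cost, which cannot support the cost-effectiveness conclusion that the article sets as an aim

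*Protocol article*

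**What the plan says.** Section 3 (Discussion) states the ambition: "We aim to establish the efficacy, safety, and cost-effectiveness of UEMR based on robust results from the D-CURE trial". The Abstract and section 2.11 go further and describe UEMR, before any data, as more cost-effective than CEMR because it needs no submucosal injection.

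The endpoint behind this is item 11 of section 2.9.2, device cost. On population: "The total cost is calculated for all treated cases". On content, it includes "single-use devices (snare, ESD knife, hemostatic forceps, injection needle, injection fluid, submucosal injection fluid, clips, and OTSC) used during endoscopic resection". On prices: "Device costs will be calculated based on Japanese reimbursement prices for single-use devices". Section 2.13.1 (item 2d) analyses it with summary statistics per group and a Wilcoxon rank-sum test. No other cost or economic analysis is described.

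Each technique depends on a fluid. For CEMR, section 2.7.1 says: "Submucosal injections must be administered with a solution commonly used at each institution". For UEMR, section 2.7.2 says: "the duodenal lumen must be filled with saline solution". If the allocated method is not completed, section 2.7.5 says that the endoscopist "may switch to an alternative treatment method, such as CEMR, UEMR, ESD, or surgical resection".

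**The concern.** Cost-effectiveness is a statement about cost in relation to outcome, over a period long enough to include the consequences of the choice. The defined endpoint stops at the devices used in the resection and is never set against recurrence, adverse events or surgery.

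The gap matters more than usual here because of how the margin is argued. Section 2.10 accepts up to 5 percentage points of extra recurrence in exchange for procedural advantages of UEMR. A cost result that includes the saving from skipping injection, but not the treatment of any added recurrence, shows one side of that trade. If it were then reported as cost-effectiveness, readers would take it to cover both sides.

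A lesser issue is that the list names the items for submucosal injection but not the fluid that defines UEMR.

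**Working it through.** The article gives no unit prices, quantities or expected cost difference, so there is no cost figure to reproduce. The check sets the sections side by side.

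**1. Is cost linked to outcome?** Section 2.13.1 specifies only group summaries and a rank test for device cost. There is no ratio, no net-benefit measure and no joint presentation with the primary endpoint. A rank-sum test also does not estimate a difference in mean cost, and it gives little weight to a few very expensive cases. The answer is no.

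**2. What does the total include?**

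| Cost source | Where the article allows or describes it | In the device-cost total? |
|---|---|---|
| Devices used in the allocated resection | 2.7.1, 2.7.2 | Yes |
| Endoscopic rescue by CEMR, UEMR or ESD | 2.7.5 | Yes, for listed items (knife, needle, fluids, clips, OTSC) |
| Surgical rescue | 2.7.5 | No; only listed devices used endoscopically beforehand |
| Treatment of delayed bleeding or perforation | 2.9.2, item 3 | No |
| Repeat endoscopic resection of a recurrence | Section 3 | No |
| Surgery for a recurrence | Section 1 | No |

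**3. Is each arm's fluid charged?** Injection fluid and submucosal injection fluid are named. Immersion saline, mandatory under section 2.7.2, is not.

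**4. Scale of what the margin permits.** The 144 per arm follows from section 2.10 (97% in both arms, margin 0.05, one-sided alpha 0.05, power 80%):

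n = (1.645 + 0.842)² × 2 × 0.97 × 0.03 / 0.05² ≈ 144 per arm, so 288 in total, and 288 / 0.9 = 320. This matches the article.

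At the margin, 0.05 × 144 = 7.2 extra events in the UEMR arm, and any re-treatment of them would add nothing to device cost. This is the boundary of the null hypothesis. Under the design assumption of equal rates the expected excess is 0.

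**The case against.** The endpoint is labelled honestly as device cost wherever it is defined or analysed, and index-procedure device cost is a legitimate secondary endpoint. Cost-effectiveness as an aim is a single Discussion sentence, and the Abstract and section 2.11 give an expectation rather than a result. This stands in part: the fault lies in the conclusion announced, not in measuring device cost. It does not remove the mismatch, because no other analysis in the article could deliver that aim.

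A reader might infer three stronger things that the document does not support.

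- *That the comparison favours UEMR by construction.* Cost covers all treated cases, and the list includes the ESD knife, needle, fluids, hemostatic forceps, clips and OTSC, so a UEMR case rescued by CEMR or ESD is charged for them. Section 2.5 cites lower en bloc rates for UEMR (81.5% against 91.3% at 10–14 mm; 62.0% against 74.4% at 15–19 mm), so listed rescue costs could fall more on UEMR. The needle and injection fluid are a real difference between the techniques. The retrieval net and the line for closure are also unlisted, but both may be used in either arm: retrieval is the same in both, and section 2.7.4 says without distinction that "the line-with-clip method or an over-the-scope clip (OTSC) is permitted".
- *That the missing saline is a material bias.* The list is introduced as what the cost includes, so it may not be exhaustive, and the generic injection fluid item is undefined. Saline is probably cheap, though no price is given.
- *That about 7 uncosted recurrences should be expected.* That number is the null boundary, as shown above.

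**Conclusion.** The concern holds as a mismatch between aim and endpoint. The trial can compare single-use device cost at the index procedure. It cannot establish cost-effectiveness, because cost is not related to outcome and surgical rescue, delayed adverse events and re-treatment of recurrence are excluded. A perfectly symmetric item list would not change this.

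The unlisted immersion saline is a genuine but minor asymmetry. Neither effect can be expressed in yen from the article, and the direction of the omitted costs is not known in advance.

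The conclusion assumes that the endoscopic resection in the cost definition means the index procedure; the article describes no collection of device data from later procedures. The primary endpoint, its analysis and the sample size are not affected.

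**What to change.** 1. In the Abstract, section 2.11 and section 3, replace the cost-effectiveness wording with index-procedure device cost, and limit the trial's economic conclusion to that.
2. Add immersion saline to the costed items in section 2.9.2, so that each arm's defining fluid is charged.
3. Report device cost beside results the trial already records: 1-year recurrence (primary endpoint), surgical duodenal resection within one year (secondary endpoint 10) and adverse events to 28 days (secondary endpoint 3). State that the costs of re-treatment and surgery are not captured.

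A second cost total running to the 12-month endoscopy is not recommended. Section 2.8 schedules the follow-up endoscopy at 12 ± 2 months, so most recurrences would be found there and treated afterwards, outside such a total. It would also need device data that the article does not show being collected.

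The cost is small: wording, one added item and a reporting table. The article does not show whether saline volume is recorded; if it is not, a stated standard quantity could be assumed. The study is expected to end by 30 November 2027, so the definitions can be settled before analysis. The downside is a narrower claim and a slightly smaller apparent saving for UEMR.

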### 2.10. Sample Size Calculation

The sample size is calculated based on the primary endpoint, 1-year RFS, to assess the non-inferiority of UEMR to CEMR.

Based on previous studies, the histological complete resection rate of CEMR for SNADET is reported to be 92–100% [2,14,24]. However, these reports are all retrospective studies with relatively short follow-up durations, which could result in a lower 1-year RFS. In this trial, the 1-year RFS in the standard treatment (CEMR) group is set at 97%. Additionally, the non-inferiority margin is set at 5%. This margin was defined as the maximum acceptable absolute excess risk of recurrence at 1 year. Prior studies of endoscopic resection for SNADETs reported very low recurrence rates under standard management. In this low-event-rate setting, an absolute margin is considered clinically interpretable. The prespecified margin of 5% was determined through multidisciplinary clinical consensus, balancing a small allowable increase in recurrence risk against the anticipated procedural advantages of UEMR.

Although the significance level of the trial is typically one-sided at 0.025 [25], the probability of decision-making error in the population with tumors at 0.05 (1 out of 20) is not considered unreasonably high according to clinical trial principles. Considering that a one-sided significance level of 0.05 was accepted in previous studies on rare diseases [12], a one-sided significance level of 0.05 is set for this study. This significance level was selected to maintain statistical feasibility in a rare disease setting with an expected extremely low event rate.

Based on these considerations, assuming a 1-year RFS of 97% for CEMR and expecting UEMR to perform equivalently, with a one-sided α error of 0.05, a non-inferiority margin of 5%, and ensuring 80% statistical power, the required sample size was calculated to be 288 cases for conducting a non-inferiority test. Considering ineligible cases and an approximately 10% dropout rate, the target enrollment number was set at 320 cases.

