#### 2.13.1. Analysis of Efficacy

The analysis of efficacy will be based on the FAS as the primary analysis population. A similar analysis will be conducted separately for the PPS. Subgroup analysis will also be performed according to preoperative biopsy status (present vs. absent), tumor length (<10 mm vs. ≥10 mm), and lesion location (bulb vs. other portions), which are allocation adjustment factors. Furthermore, an analysis of cases of untraceability (missing values) will be conducted, considering the inability to perform follow-up EGD.

Analysis of primary endpoint

The 1-year RFS, the primary endpoint, will be aggregated for each group, and the intergroup difference and the 95% confidence intervals (CI) will be calculated. The null and alternative hypotheses for the non-inferiority test are as follows:

Null hypothesis: 1-year RFS of UEMR, P1 + Δ ≤ 1-year RFS of CEMR, P2 (UEMR is inferior to CEMR by more than Δ)

Alternative hypothesis: 1-year RFS of UEMR, P1 + Δ > 1-year RFS of CEMR, P2 (UEMR is not inferior to CEMR by more than Δ)

If the null hypothesis is rejected at a one-sided 5% significance level in the non-inferiority test, we will conclude that UEMR is not inferior to CEMR. If non-inferiority in the 1-year RFS is demonstrated in the primary analysis, a test for superiority will be conducted.

2.Analysis of Secondary Endpoints
a.*En bloc* resection rate, histological complete resection rate, technical success rate, complete mucosal closure rate, and complete mucosal closure rate with standard clips: The rates for the CEMR and UEMR groups, the point estimate of the intergroup differences, and the 95% CI will be calculated.b.Total procedural, resection, and mucosal closure times: Summary statistics will be computed for both groups. The Wilcoxon rank-sum test will be used.c.One-year duodenum preservation survival rate: The rates for the CEMR and UEMR groups, the point estimate of the intergroup difference, and the 95% CI will be calculated.d.Device cost: Summary statistics will be computed for each group, and the Wilcoxon rank-sum test will be used for comparison.

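### At 288 patients the stated 80% power and one-sided 5% error do not hold together: tests that keep about 5% have about 72% power (about 77% if all 320 are analysed)

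*Protocol article*

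**What the plan says.** Section 2.10 (Sample Size Calculation) fixes every design input. The control rate is an assumption: "the 1-year RFS in the standard treatment (CEMR) group is set at 97"%. The UEMR arm is given the same rate ("expecting UEMR to perform equivalently"). The margin is 5 percentage points and "a one-sided significance level of 0.05 is set for this study". From these it derives "a non-inferiority margin of 5%, and ensuring 80% statistical power, the required sample size was calculated to be 288 cases", then raises the target to 320 for ineligible cases and about 10% dropout. No formula is named.

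Section 2.13.1 (Analysis of Efficacy) applies the same level to the decision: "If the null hypothesis is rejected at a one-sided 5% significance level in the non-inferiority test", UEMR is declared non-inferior. For the estimate, "the intergroup difference and the 95% confidence intervals (CI) will be calculated". The test statistic and interval method are not named, which is a matter an analysis plan may settle.

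Section 2.9.1 (Primary Endpoint) takes all treated cases as the denominator and counts patients who cannot be followed by endoscopy as non-recurrent.

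**The concern.** At 97% RFS each arm of 144 is expected to have 144 × 0.03 ≈ 4.3 events. The normal approximation to a difference of two proportions is poor with so few events, and here it errs in the liberal direction: the estimated standard error tends to be too small when the observed rates look close together. A sample size taken from that approximation describes a test that does not keep its nominal level, while a test that does keep the level needs more patients for the same power.

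The level matters in this trial. Section 2.10 acknowledges that one-sided 0.025 is typical and argues for accepting an error of 1 in 20. If the real error is about 6.2%, it is nearer 1 in 16. If the real error is 5%, the chance of missing true non-inferiority is about 28% at 288 rather than 20%.

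**Working it through.** **Inputs.** CEMR RFS 0.97, UEMR RFS 0.97, margin 0.05, one-sided α 0.05, power 0.80 (all Section 2.10); 1:1 allocation (Section 2.5).

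**1. The plan's own figure.** With the unpooled normal-approximation formula,

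n per arm = (z₀.₉₅ + z₀.₈₀)² × [p₁(1−p₁) + p₂(1−p₂)] / margin²
= (1.6449 + 0.8416)² × (2 × 0.97 × 0.03) / 0.05²
= 6.183 × 0.0582 / 0.0025 = 143.9.

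This gives 144 per arm and 288 in total, and 288 / 0.9 = 320. Both stated figures reproduce.

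**2. Exact operating characteristics.** For each candidate test, sum the two binomial distributions over all pairs of outcomes that reject. Power is taken at equal rates. One-sided error is taken at the margin, with UEMR 5 points below CEMR.

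At 144 per arm:

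| RFS (CEMR) | Wald power | Wald error | Score power | Score error |
|---|---|---|---|---|
| 95% | 62% | 5.7% | 58% | 5.0% |
| 96% | 71% | 5.8% | 64% | 4.8% |
| **97%** | **80.0%** | **6.2%** | **72.4%** | **4.6%** |
| 98% | 89% | 6.8% | 83% | 4.4% |
| 99% | 98% | 7.2% | 93% | 4.2% |

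A simulation of 2,000,000 trials at 92% versus 97% also gives 6.2% for the Wald error.

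**3. Other tests at 144 per arm, 97% design rate.**
- Pooled-variance normal test: same power and same error as the unpooled one.
- Miettinen-Nurminen and Newcombe: 72.4% power, 4.6% error.
- Exact unconditional test with score ordering (error at most 5% everywhere): 72.3% power.
- Continuity-corrected Wald: 70.3% power.
- Agresti-Caffo: 77.6% power, but 5.5% error.
- Wald with its cut-off raised to give 5% at exactly 97%/92%: 76.7% power. Raised to give 5% over CEMR 95% to 99%: 72.4%.

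No test examined reaches 80% at 288 while keeping 5%.

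**4. If more than 288 are analysed.** At 160 per arm (all 320), 97% design rate:
- Score: 77.4% power, 4.6% error.
- Wald: 83.9% power, 6.1% error.

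If in addition 10% of outcomes are missing and counted as non-recurrent, the apparent rate becomes 0.97 + 0.1 × 0.03 = 0.973 and score power is 80.2%. The same rule shrinks a true 5-point deficit to 0.9 × 5 = 4.5 points (92.8% versus 97.3% apparent). At that point the score test at 160 per arm rejects 6.9% of the time, so this route to 80% does not keep 5% for the true difference either.

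**5. Size needed.** Exact score power first reaches 80% at about 176 per arm (352). The asymptotic Farrington-Manning formula gives 183 per arm (366).

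**6. A case where the choice decides the result.** Take 144 per arm with 4 CEMR events and 6 UEMR events. The difference plus margin is 138/144 − 140/144 + 0.05 = 0.0361.
- Wald standard error: √[(0.9583 × 0.0417 + 0.9722 × 0.0278)/144] = 0.0216, so z = 1.67 > 1.645 and non-inferiority is declared.
- Score: the rates fitted under the margin constraint are 0.9305 and 0.9805, the standard error is 0.0241, and z = 1.50, so it is not declared. The score test accepts at most 5 UEMR events here.

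**The case against.** **The arithmetic is right.** A reader might infer that 288 is a calculation error. It is not; 288 and 320 both reproduce. The issue is the power and error that 288 delivers.

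**The test is not named, and need not be here.** This stands as far as it goes. A reader might infer that the trial will run at 6% to 7% error, or that leaving the test unnamed is itself a defect. The article supports neither: the analysis plan may specify a score or exact test, and the inflated error arises only with a Wald-type analysis. But the stated pair does not hold at 288 either way. A Wald-type test loses the 5%; a level-keeping test loses the 80%.

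**288 is not the number analysed.** This is largely fair. Target enrolment is 320, and under Section 2.9.1 loss to endoscopic follow-up does not remove a patient. Section 2.13 still excludes ineligible, erroneously enrolled, no-data and untreated patients from the full analysis set, so the analysed number lies somewhere up to 320. Quoting 72% alone would therefore be too harsh; the range is about 72% to 77%. The step to 80% depends on counting unobserved outcomes as successes.

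**A better event rate rescues power.** True: at 98% RFS the score test has 83% even at 288. At 95% it has 58%. Hence a table rather than a single figure.

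**The basis for 97%.** Section 2.10 introduces the rate after noting that "the histological complete resection rate of CEMR for SNADET is reported to be 92–100"%, and a reader might infer that 97% rests on the wrong endpoint. The section itself warns that RFS could be lower and presents 97% as a set value, so nothing further follows for this point.

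**The Discussion already counsels caution.** It promises sensitivity analyses with stricter margins and emphasis on intervals. That helps interpretation but does not correct the stated power.

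**Conclusion.** The concern holds as a matter of design and power. With 97% RFS in both arms, a 5-point margin and 288 analysed, the normal-approximation test behind the sample size has 80.0% power but a true one-sided error of 6.2% (5.7% to 7.2% for CEMR RFS of 95% to 99%). Tests that hold about 5% have 72.3% to 72.4% power. With all 320 analysed, score power is 77.4%.

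The figures rest on the plan's own rates, equal arms and independent binomial outcomes. The score and Newcombe tests peak at about 5.3% somewhere in the full null space, but at 144 per arm they stay below 5% for CEMR RFS of 95% to 100%; the exact unconditional version, which never exceeds 5%, gives the same power to within 0.1 point.

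The shortfall is moderate: about 8 points at 288 and 3 points at 320. It calls for a correction of the stated properties, not for a different trial.

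**What to change.** Specify the Farrington-Manning (Miettinen-Nurminen) score test for the primary non-inferiority comparison, with the matching score interval for the difference. Do this before the primary analysis, since enrolment has begun.

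Keep the target of 320. Restate power at one-sided 5% as about 72% with 288 analysed and about 77% with 320, and add a short table of score power:

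| RFS in both arms | 288 analysed | 320 analysed |
|---|---|---|
| 95% | 58% | 61% |
| 96% | 64% | 69% |
| 97% | 72% | 77% |
| 98% | 83% | 87% |

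The cost is analysis-plan wording and a less favourable stated power. No additional patients are required. Restoring 80% at a kept 5% level would take about 352 analysed patients, which this fix does not ask for.
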